### **8.4 Schedule of visits and evaluations**

The baseline visit will be made to the patients after selection by their responsible physician. Additionally, patients will be visited at 6 and 12 months. A last visit will be made at 24 months to the patients who continue in the study. The data that will be collected at each time point is shown in **Table 2** of section 6.6.

### **8.5 Procedures for each visit**

#### **8.5.1 Selection visit**

Potential patient candidates for participation in the study will be selected opportunistically during medical consultations (case-finding) by the physicians responsible for the patients, known as Family Physician Investigators (MEFI). Ideally, MEFIs will aim to select one patient per day, every day of the week, until they reach the required number of patients for each MEFI.

During the same medical consultation at the Healthcare Center, MEFIs will inform patients about the study's objectives. If patients meet the inclusion criteria and none of the exclusion criteria (confirmed through electronic medical records and discussions with the patient and at the discretion of the doctor), they will be provided with an information sheet and an informed consent form. Patients will be given a private room to carefully review these documents at their own pace, with ample time provided if needed, and any questions they have will be answered.

To confirm the inclusion criteria related to hypertension (systolic blood pressure >140 mm Hg or diastolic blood pressure >90 mm Hg), the MEFI will measure blood pressure using a validated sphygmomanometer in accordance with the recommendations of the Guidelines for the management of arterial hypertension provided by the Task Force for the management of arterial hypertension of the European Society of Hypertension and the European Society of Cardiology (**Table 3**).

**Table 3. MEASUREMENT OF BLOOD PRESSURE IN THE OFFICE**

|                                                                                                                                                                                                                                        |
|----------------------------------------------------------------------------------------------------------------------------------------------------------------------------------------------------------------------------------------|
| When blood pressure (BP) is taken in the office, the following considerations should be taken into account                                                                                                                             |
| The patient must remain seated for 3-5 minutes before taking the blood pressure.                                                                                                                                                       |
| At least 2 measurements should be taken in the sitting position, spaced 1-2 minutes apart, or an additional measurement if the first 2 are quite different. The average of the 2 measurements taken as valid will be considered as TA. |
| Use standard sleeves but also have larger and smaller sleeves for wider and smaller arms.                                                                                                                                              |
| Place the cuff at the level of the heart, whatever the position of the patient.                                                                                                                                                        |
| Take the BP in both arms at the first visit to detect possible differences. If they are, take the arm with the highest BP as the reference arm.                                                                                        |
| Measure the first BP after standing for 1 to 3 minutes in elderly, diabetic or other patients with suspected orthostatic hypotension.                                                                                                  |

Modified from Mancia G et al. J Hypertension. 2013.

For each patient, once it has been verified that the inclusion criteria are met and the exclusion criteria are not met, and once the informed consent is signed, the MEFI will enter into the web system and under mandatory guarantees of information security, the information of identification of the patients, marking the boxes corresponding to meeting the inclusion criteria and not meeting the exclusion criteria, and the information necessary for randomization with minimization (see 6.3.1 for more details on the minimization process). The MEFI will receive the result of the randomization and the anonymization code assigned to the patient via the Web, and the patient will be included in an electronic patient identification form with restricted access to Collaborating Research Physicians (MIC). The patient identification form will not contain any health data or other sensitive information. All the documents in which the data of the patients in the framework of the ADAMPA study are recorded (CDR, Patient's Notebook) will be identified only by the code assigned to each patient. Likewise, and in order to help their adequate follow-up and identification in the consultation, it will be indicated in the electronic medical record that the patient participates in the ADAMPA STUDY.

All patients, both those randomized to the control group and those in the intervention group, will receive information from the MEFI that a collaborating research physician (MIC team) will contact them by telephone to schedule the baseline visit.

Furthermore, the MEFI will provide all patients with an ADAMPA study Patient's Notebook. On the first page, the assigned patient code will be recorded. In the case of the intervention group, the MEFI will also note on the first page the arm in which the patient's blood pressure will be measured and their target figures. The Intervention Group Notebook will contain:

- First sheet: patient anonymization code, arm for blood pressure measurement, target figures
- Information about the importance of hypertension and lifestyle advice
- Instructions on how to take your blood pressure at home
- Instructions on how to act based on the voltage figures at home
- The medication self-adjustment plan established by the MEFI. The MEFI may establish the initial self-adjustment plan on that same visit or on another scheduled visit agreed upon with the patient.
- Sheets for recording BP values and for recording care contacts with your Health Center.

In turn, the Patient's Notebook for the control group will contain:

- First sheet: patient anonymization code, arm for taking blood pressure
- Information about the importance of hypertension and lifestyles
- Sheets for recording care contacts with your Health Center

#### 8.5.2 Baseline visit

- Intervention group: the baseline visit will include the training intervention (described in section 6.4) and data collection (contained in Table 2 of section 6.6). Additionally, they will be informed that periodic group sessions will be held with the patients (in charge of the MICs) to reinforce the BP measurement technique, its recording and the self-adjustment plan.
- Control group will consist solely of data collection (consisting in **Table 2** of section 6.6). They will be told that they must follow their usual medical and nursing check-ups.

All patients, regardless of group, will be provided with a follow-up date at 6 months, informing them that they will be reminded beforehand by telephone and that they must come with the completed Patient Notebook.

If the patient does not attend the baseline visit, the patient will be located by telephone to give a new visit date or, in the event that they are not located or abandon the study, the date and the reason for it will be recorded.

The estimated period for the recruitment and first visit of the patients in the sample is estimated at 3 months.

Any data collected from patients that does not appear in their medical history will be added.

#### 8.5.3 Follow-up visits

- 6-Month Visit:
  - o Researchers will record data related to the variables of the follow-up visit (as outlined in **Table 2** of section 6.6). Data sources will include information provided by the patient, the Patient's Notebook, and the patient's electronic medical record.
  - o All patients, regardless of their group, will receive a 6-month follow-up appointment and will be informed that they will receive a reminder call beforehand. They should also bring their completed Patient's Notebook.
- 12-Month Visit:
  - o Researchers will collect data related to the variables of the follow-up visit (as detailed in **Table 2** of section 6.6), using information from the patient, the Patient's Notebook, and the electronic medical record.
  - o Patients, irrespective of their group, will be informed that they will continue with their group-specific trial instructions (self-monitoring/self-adjustment or usual care). Simultaneously, they will maintain their regular medical and nursing appointments. They will also be informed that they will receive a phone call for a final visit within a year and should bring their completed Patient's Notebook.
- 24-Month Visit:
  - o During this visit, a reduced set of outcome variables will be collected, including blood pressure, quality of life, and use of healthcare services (as outlined in **Table 2** of section 6.6).
  - o The purpose of this visit is to conduct secondary analyses after a period of passive follow-up. This aims to evaluate adherence to the intervention under conditions even closer to usual clinical practice. Additionally, results at 24 months will be obtained during this visit.

- During the period from months 12 to 24, MICs will not provide reminders, and nurses will carry out complementary assistance work alongside MEFIs for follow-up, adjustment plan renewals, etc.

If the patient does not attend the follow-up visits, the patient will be located by telephone to give a new date of visit or, in the event that he is not located or leaves the study, the date and the reason for it will be recorded. Any data collected from patients that does not appear in their clinical history will be included in it.

#### 8.5.4 Final visit

The visit at 12 months is the visit considered the final visit in the strict sense of the trial and with which data the main analyzes will be carried out. The 24-month visit will be carried out after passive follow-up to assess adherence (and effectiveness) to the intervention in conditions even closer to usual clinical practice.

#### 8.5.5 Treatment visit

Visits to modify treatment, if applicable, will be carried out in the usual context of clinical practice by the patient's family doctor (MEFI) in both the control and intervention groups.

Additionally, the patients of the Intervention group will make visits or telephone consultations to their MEFI when so indicated according to the mode of action according to blood pressure figures, in the event that they must proceed to self-adjust the medication according to the plan. self-adjustment established by the MEFI and registered in the patient's notebook.

In the event that a patient from the intervention group, and based on their objective figures and the instructions received, has to proceed to the self-adjustment at home, they will again follow the mandatory instructions and that are also included in the Patient's Notebook and You will request an appointment with your MEFI within a maximum period of three weeks. On said visit after self-adjustment, the MEFI will review the patient's condition and renew the self-adjustment plan, recording said new self-adjustment plan in the Patient's Notebook.

## **9. EFICACY ASSESSMENT**

### 9.1 Efficacy variables and evaluation methods

**Table 4. Efficacy variables (comparative effectiveness) of the ADAMPA study**

| VARIABLES                                                                                                                                                                                           | EVALUATION METHODS                                                                                                                                                                                                                                                                                                                                      |
|-----------------------------------------------------------------------------------------------------------------------------------------------------------------------------------------------------|---------------------------------------------------------------------------------------------------------------------------------------------------------------------------------------------------------------------------------------------------------------------------------------------------------------------------------------------------------|
| Primary outcome measure                                                                                                                                                                      |                                                                                                                                                                                                                                                                                                                                                         |
| Difference in mean systolic blood pressure (SBP), in mmHg at 12 months of follow-up between the intervention and control groups.                                                                    | It will be determined at physicians' practice with a validated automatic electronic sphygmomanometer.

At least 2 measurements will be taken in a seated position, spaced at 1-2 minutes, and another additional measurement if the first 2 are very different. The average of the measurements taken  will be considered as SBP/DBP. |
| Secondary outcome measures                                                                                                                                                                   |                                                                                                                                                                                                                                                                                                                                                         |
| Difference in mean SBP, in mmHg at 6 and 24 months of follow-up between the intervention and control groups.                                                                                        | It will be determined at physicians' practice with a validated automatic electronic sphygmomanometer.

At least 2 measurements will be taken in a seated position, spaced at 1-2 minutes, and another additional measurement if the first 2 are very different. The average of the measurements taken  will be considered             |
| Difference in mean diastolic blood pressure (DBP), in mmHg at 6, 12 and 24 months of follow-up between the intervention and control groups.
It will proceed in the same way and at the same time |                                                                                                                                                                                                                                                                                                                                                         |

|                                                                                                                                                               |                                                                                                                                                                                                                                                                                                                                                                               |
|---------------------------------------------------------------------------------------------------------------------------------------------------------------|-------------------------------------------------------------------------------------------------------------------------------------------------------------------------------------------------------------------------------------------------------------------------------------------------------------------------------------------------------------------------------|
| as with the SBP                                                                                                                                               | as SBP/DBP.                                                                                                                                                                                                                                                                                                                                                                   |
| Difference in the percentage of patients with SBP <140 mmHg and DBP <90 mmHg at 6, 12 and 24 months of follow-up between the intervention and control groups. |                                                                                                                                                                                                                                                                                                                                                                               |
| Health-related quality of life (HRQoL) at 6, 12 and 24 months of follow-up.                                                                                   | The EuroQoL-5D questionnaire will be used to assess the impact of the intervention on the quality of life of the patients compared to the control group.                                                                                                                                                                                                                      |
| Between-group difference in Proportion of days covered with medication (PDC)                                                                                  | Secondary adherence (PDC and persistence) will be estimated using the prescription and dispensing data obtained from the Department's databases and the definitions detailed in section 6.1 will be applied.                                                                                                                                                                  |
| Difference Between Groups in Persistence                                                                                                                      |                                                                                                                                                                                                                                                                                                                                                                               |
| Difference between groups with respect to Therapeutic Inertia (IT)                                                                                            | Quotient between the number of patients whose pharmacological treatment has not been changed divided by the number of patients with SBP and/or SBP measurements taken in consultation at 6, 12, and 24 months of follow-up above the values target according to the recommendations of the European Society of Hypertension and European Society of Cardiology  . |
| Other outcome measures (tertiary endpoints):                                                                                                           |                                                                                                                                                                                                                                                                                                                                                                               |
| Differences in changes in lifestyles (smoking, exercise, weight) at 6, 12, and 24 months with respect to the baseline measurement.                            | Changes in lifestyles will be evaluated based on the information collected at follow-up visits.                                                                                                                                                                                                                                                                               |
| Difference between groups in relation to the occurrence of adverse events: angina, myocardial infarction, stroke, hypotensive crisis and death.               | Hospitalizations due to adverse events will be collected at follow-up visits. Outpatient and emergency visits due to hypotensive crises will also be collected.                                                                                                                                                                                                               |
| Differences in the use of health services during follow-up (6, 12 and 24 months).                                                                             | Including HTA-related primary medical and nursing care consultations (at the center by appointment or without an appointment, by telephone and at home). Visits to emergency hospital services, hospital admissions, hospitalization days per admission and main diagnosis                                                                                                    |
| Incremental cost per additional quality-adjusted life year gained in the intervention group compared to the control group.                                    | Cost-consequence analysis and cost-effectiveness analysis                                                                                                                                                                                                                                                                                                                     |
| Assessment of the intervention by the patients and the research family physicians.                                                                            | Focus groups with patients and professionals involved (MEFI, MIC and nurses)                                                                                                                                                                                                                                                                                                  |

Complementary tests (functional, laboratory, radiological, etc.) in addition to those carried out in regular clinical practice to assess efficacy will not be performed.

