#### **6.1.2 Secondary outcome measures**

1. Difference in mean systolic blood pressure, in mmHg at 6 and 24 months of follow-up between intervention and control groups determined at physicians' practice with a validated automatic electronic sphygmomanometer.
2. Difference in mean diastolic blood pressure, in mmHg at 6, 12 and 24 months of follow-up between intervention and control groups determined at physicians' practice with a validated automatic electronic sphygmomanometer.
3. Percentage of patients with SBP <140 mmHg and DBP <90 mmHg at 6, 12 and 24 months of follow-up.

4. Quality of life (as measured by EuroQoL-5D) at 6, 12 and 24 months of follow-up.
5. Adherence measured by proportion of days covered (PDC) at 6 and 12 months of follow-up.
6. Persistence, defined as period of continuous use of the corresponding drug from the beginning of the follow-up until its discontinuation at 6 and 12 months of follow-up.
7. Therapeutic inertia (TI), defined as the number of patients whose pharmacological treatment had not been modified, divided by the number of patients not reaching the target values (SBP and/or DBP measurements taken at 6 and 12 months of follow-up), according to the recommendations of the European Society of Hypertension and European Society of Cardiology (19).

Other outcome measures:

1. Changes in lifestyle (smoking, exercise, body weight) at 6, 12, and 24 months compared to these characteristics at baseline.
2. Clinical events: We will assess if any of the following adverse events are present during the follow-up: angina, myocardial infarction, stroke, hypotensive crisis and death.
3. Use of health services for hypertension at 6, 12 and 24 months.
4. Incremental cost per quality-adjusted life year gained in the intervention group compared to the control group.
5. Views and experiences of patients and health professionals on the self-management (SMBP plus self-titration) of hypertension.

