#### **6.5 Patients follow-up**

The follow-up of the patients will be conducted by the MEFIs in line with routine clinical practice conditions. MEFIs will be responsible for patient selection and inclusion in the trial and will execute the training actions as outlined in point 6.4.

Additionally, the MIC team will reinforce the training and information actions specified by the MEFI and defined in point 6.4. However, it's important to note that the MIC team will not make clinical decisions or modify the management or recommendations of the MEFI. They will also handle data collection during the scheduled visits in the study, including the baseline visit and follow-up visits at 6 and 12 months, working in collaboration with the MEFI.

In the first 12 months of the study, the MIC team will conduct bi-monthly telephone reinforcement sessions. These sessions aim to contact patients in the intervention group with the goal of improving adherence to the intervention and addressing any potential concerns.

In the second year (passive or pragmatic follow-up), patient follow-up will be aligned as closely as possible with routine management in usual clinical practice. Therefore, the role of the MIC will be carried out by a nurse

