#### **6.6 Identification of the data to be recorded**

The MEFIs, in collaboration with the MICs, will be responsible for collecting data at each of the Health Centers during the baseline and follow-up visits. The MICs will work in agreement and in cooperation with the MEFIs. It's important to note that the MICs will not make any clinical decisions regarding the patients participating in the study; this responsibility solely rests with the MEFI.

In cases where, during the baseline or follow-up visits, the MICs obtain additional health-related information from the patients (such as medical history or comorbidities) or acquire more recent study variables than those recorded in the patient's electronic medical record (e.g., BMI, blood pressure), they will include this information in the patient's clinical history. To facilitate this process, a meta-profile will be created (ADAMPA study), ensuring that all patient information (study variables) used in the trial is accurately reflected in the patient's medical record.

The data will be recorded in the visits -baseline, at 6 months, the final at 12 months and the extension at 24 months in the Data Collection Notebook (CDR) prepared for this purpose. The CDR will be completed in computer support. The sources to obtain the necessary data for the study will be:

- The electronic medical record of the Ambulatory Information System –SIA- (ABUCASIS) available in all Health Centers.
- The ORION program that allows access to the electronic hospital medical record.
- The clinical interview with the patient at the established visits (baseline, at 6, 12 and 24 months).
- Information on paper: serious adverse events and self-monitoring and self-adjustment booklet.
- Additional information will be extracted from the Valencia Health System electronic databases: Minimum Basic Data Set (MBDS), ABUCASIS and the Population Information System (SIP).

The following information will be collected at each visit.

Table 2. Data collection throughout the trial

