**Serious adverse events that do not require immediate notification by the investigator**

The following serious adverse events do not require immediate notification by form:

- Thromboembolic events (deep vein thrombosis, pulmonary thromboembolism)
- Neurological events (stroke, cerebrovascular accident, acute confusional syndrome)
- Cardiological events (angina, myocardial infarction, cardiac arrhythmia, decompensation of heart failure, hypotensive crises)
- Impaired renal function
- Gastrointestinal bleeding
- Need for blood transfusion
- Hospitalization due to hydroelectrolyte disorder

In any case, there will be a section in the CRD to collect information on possible serious adverse events reported by the patient during follow-up visits. Serious adverse events that do not require immediate notification must be included in the clinical history and in the CRD, and will be included in the periodic safety report.

On the other hand, the study will collect data related to urgent hospital admissions due to episodes of angina, myocardial infarction, stroke, and hypotensive crises, as well as death from any cause, along with outpatient and emergency visits due to hypotensive crises, as part of the tertiary objectives of the study. Given the characteristics of the included population (and the results of the TASMINE-SR^17 study), figures of less than 3% are expected for the combined endpoints; therefore, it is not anticipated that differences will be detectable. For these serious events, as well as for deaths, the Family Physician Investigators responsible for the patients (MEFI) will review the medical history and determine their potential relationship with the intervention. Previous trials have failed to find any evidence of such a relationship.

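### Non-fatal clinical events are tied to follow-up visits and no event search is required for patients who stop attending, although suitable record sources are already listed

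*Protocol*

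**What the plan says.** Section 6.1.2 of the protocol defines the outcome by what happens over the whole of follow-up: "We will assess if any of the following adverse events are present during the follow-up", followed by angina, myocardial infarction, stroke, hypotensive crisis and death. Table 4 (section 9.1) gives the method: "Hospitalizations due to adverse events will be collected at follow-up visits". It then adds a second component without a source or a timing: "Outpatient and emergency visits due to hypotensive crises will also be collected". Table 2 (section 6.6) lists adverse events among the data of the 6-, 12- and 24-month visits.

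The adherence row of Table 4 is handled differently: "Secondary adherence (PDC and persistence) will be estimated using the prescription and dispensing data obtained from the Department's databases". That source does not depend on attendance.

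Section 6.6 names ABUCASIS and the hospital record through ORION as data sources, and continues: "Additional information will be extracted from the Valencia Health System electronic databases", meaning MBDS, ABUCASIS and SIP. It does not say which of these supplies the clinical events. Section 12.2 obtains permission to consult the clinical history for clinical outcomes and resource use.

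On absence, section 7.4 invites all participants, including those who discontinue, to the scheduled visits. Section 8.5.3 has non-attenders telephoned; if they are not located or have left, it mentions only the date and reason. Section 8.4 limits the 24-month visit to patients still in the study.

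**The concern.** The outcome is defined over follow-up, but the stated method works through visits. The event itself can cause the absence: section 7.3.2 lists an adverse event or disease progression that prevents trial procedures among the reasons for discontinuation. A comparison confined to attenders is a comparison of groups selected after randomisation, and it departs from the intention-to-treat principle of section 7.4 for an outcome that could be followed without a visit.

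Hypotensive crisis is an obvious harm to examine when patients adjust their own antihypertensive treatment. Clinical events also enter the cost-consequence analysis and the longer-term model in section 11.2, and section 12.6 ties interruption of the study to differences in intervention-related serious adverse events. With very few events expected, a handful missed would be a large share of the total.

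**Working it through.** **1. The protocol's own figures (section 11.1).** Inputs: difference 5 mmHg, SD 15 mmHg, two-sided alpha 0.05, power 90%.
- Normal approximation: n per arm = 2 × (1.960 + 1.282)² × 15² / 5² ≈ 189.1, so 190 per arm (380 in all).
- With the t distribution: 191 per arm, 382 in all, power 90.1%. This reproduces 382.
- 382 × 1.20 = 458.4, reproducing 458. The allowance corresponds to 458 − 382 = 76 patients, and 76 / 458 = 16.6% lost.

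**2. Expected events.** Section 10 expects less than 3% for the combined endpoints. At that ceiling, 0.03 × 458 = 13.7 events, or 6.9 per arm.

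**3. Share missed if capture depended wholly on attendance.** Let l be the proportion not attending and RR the event risk of non-attenders relative to attenders. Then

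share missed = l × RR / [(1 − l) + l × RR].

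The documents give neither RR nor the actual proportion not attending, so both are shown as ranges, at the 3% ceiling (13.7 events):

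| Not attending | RR 1 | RR 2 | RR 3 |
|---|---|---|---|
| 5% (assumed) | 5.0%, 0.7 events | 9.5%, 1.3 | 13.6%, 1.9 |
| 10% (assumed) | 10.0%, 1.4 events | 18.2%, 2.5 | 25.0%, 3.4 |
| 16.6% (full allowance) | 16.6%, 2.3 events | 28.5%, 3.9 | 37.4%, 5.1 |

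Example, last cell: 0.166 × 3 / (0.834 + 0.166 × 3) = 0.498 / 1.332 = 37.4%; 0.374 × 13.7 = 5.1.

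**4. Between-arm effect.** With equal true rates, RR 1 and an assumed attendance of 90% in one arm and 80% in the other, the observed event ratio would be 0.90 / 0.80 = 1.125. The documents do not indicate which arm would attend more.

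**5. What the text requires for a non-attender.**
- Deaths: section 10 requires notification within 24 hours of knowledge while the subject is in follow-up. This route does not depend on a visit.
- Non-fatal components: section 10 exempts stroke, angina, infarction and hypotensive crises from immediate notification by form. They must still be entered in the clinical history and the data collection notebook, but no step tells anyone to look for them in a patient who has stopped attending.
- Medical-history review: section 10 has the family physician review the history of these events to judge their relationship with the intervention. It is not described as a search for events.

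**The case against.** The strongest reply is that visit collection is not the same as patient recall. Section 8.5.3 has the 6- and 12-month data drawn from the patient, the notebook and the electronic medical record, so the Table 4 sentence may describe when data are entered rather than the only source. The later paragraph of section 10 on the tertiary objectives describes urgent admissions, deaths and hypotensive-crisis contacts with no visit restriction. The neighbouring Table 4 row on health-service use already covers admissions with main diagnosis. Discontinued patients are still invited, and the family doctor is also the investigator. Much of this stands: it makes loss of events a risk, not a certainty. It does not supply an event search for non-attenders, and Table 2 places health-service use at the visits too.

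Three stronger readings are tempting and not supported.
- A reader might infer that section 10 relies on patient report. The words "possible serious adverse events reported by the patient during follow-up visits" describe one section of the data collection notebook, not the source of the tertiary endpoint.
- A reader might infer that the intervention arm will report more because it has more contact. The telephone calls are indeed one-sided ("These sessions aim to contact patients in the intervention group"), and section 8.5.5 adds physician contacts. But the scheduled collection visits are the same in both arms, and the calls are not named as a source for this endpoint. Unequal capture is plausible, chiefly for hypotensive episodes without admission; its direction and size are not shown.
- A reader might infer that the databases cover every patient and every event. The protocol names them without stating their coverage.

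**Conclusion.** The point holds as a gap in the stated method: non-fatal events are tied to visits, nothing requires a search for events in patients who stop attending, and sources that could provide one are already listed.

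The 2 to 5 missed events out of about 14 are an illustration near the worst case. They rest on the full 16.6% loss, the 3% ceiling, no capture at all without a visit, and assumed risk ratios of 1 to 3. At 5% non-attendance the range falls to 0.7 to 1.9 events, and it falls further if records are searched. The figures show missed events, not a demonstrated bias between arms.

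The endpoint is tertiary, section 10 already says that differences are not expected to be detectable, and the sample size is unaffected. Weight: minor to moderate, a cheap improvement.

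**What to change.** In Table 4, state that the following are extracted from the section 6.6 records and databases for every randomised patient: admissions for angina, infarction, stroke and hypotensive crisis; deaths; and emergency or outpatient visits for hypotensive crisis. Use the same windows in both arms (randomisation to 12 months and to 24 months), regardless of visit attendance, unless consent to record access is withdrawn. Keep visit reports as a supplement, name which source supplies which component, and reconcile Table 4 with section 6.6 and section 10.

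Report admitted or emergency events separately from primary-care contacts for hypotension. Record extraction does not make the latter comparable, because the intervention arm has extra physician contacts under section 8.5.5 at which such episodes can be noted.

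Cost: revised table wording and some extra extraction work. Database extraction is already planned and consent already extends to clinical outcomes in the clinical history; the sponsor should confirm that this covers the databases used. Downside: care outside the regional system may not be captured, which is why visit reports remain useful.
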